### Intervention development

2.6

The intervention program builds on a transdiagnostic CBT approach. The TA was preferred because it has a flexible and modular structure that can be easily integrated into the functioning of CBT [51,52]. The intervention program is founded on this approach and the relevant literature [34,51,58,60,69,70]. The intervention will consist of six modules. The first module's topics will be goal setting and motivation enhancement. Psychoeducation and mindfulness will be covered in the second module. The third module will focus on cognitive restructuring and other cognitive interventions. Exposure and other behavioral interventions will be the main topics of the fourth module. The fifth module will include emotion regulation strategies. Finally, the last and sixth modules will be devoted to relapse prevention strategies and termination.

### Guidance

2.7

After random assignment of participants into three groups (guided, unguided, or control), participants in the guided group will receive expert-written feedback within 24 h of each module's completion. Feedback will be delivered by researchers (guides) working on the project as scholars and these researchers/guides will receive two days of training from two specialists who are experts in CBT and TA. The researchers (guides) working on this project have been educated in psychology/counseling fields (at least a master's degree) and have previous experience in the CBT approach. All the feedback provided by guides to program users will not exceed 300 words. The feedback will not include therapeutic intervention beyond what is offered in the program, as the feedback's main goal is to encourage/motivate the participant. The other/next module will start after the feedback message has been sent. Before sending feedback to participants in the guided group, all the feedback composed by researchers/guides will be checked and approved by those who train guides to maintain consistency across researchers/guides.

Participants in the unguided group will utilize the program entirely on their own and will not receive regular feedback upon module completion. The next module will be available the day after the previous one is finished. Participants in both guided and unguided groups will receive reminder messages on the third and fifth days if they have not yet begun the next module in the program.

### Control condition

2.8

The waitlist control (WLC) group will be asked to complete pre- and post-assessments at initial registration and by the end of the eighth week. Participants will not be in contact with the research team throughout the waiting period. They will be given the unguided version of the program at the 12th week, after the completion of the assessment tools. Participants who complete all measurement tools will receive a gift card (which they can spend on numerous web pages) as a means of encouragement.

### Measurements and outcomes

2.9

Three assessments will be conducted as part of the study: baseline (T0) for all groups, immediately following program completion (T1; 8 weeks), and a follow-up four weeks following randomization (T2; 12 weeks). All participants, regardless of whether they have completed the program, will receive the assessment at T1 (8 weeks). Table 1 provides a summary of all the variables and measurements.

**Table 1 tbl1:** Summary of measurement tools.

Measurement Tool	Pilot Study	T0	T1	T2
Demographic Information Form	X	X		
Patient Health Questionnaire – 9 (PHQ-9)		X	X	X
Generalized Anxiety Disorder – 7 (GAD-7)		X	X	X
The Brief Adjustment Scale – 6 (BASE-6)		X	X	X
System Usability Scale (SUS-10)	X	X		
Attitudes Toward Internet-Based Interventions Scale (ETAM)		X		
Module Evaluation (guided and unguided group)			X	
User Experience on Program Effectiveness			X	
User Experience on Dropout			X	

#### Outcome measures

2.9.1

##### Patient Health Questionnaire-9 (PHQ-9) Turkish form

2.9.1.1

PHQ-9 was developed by Kroenke et al. [71] to gauge the symptoms and severity of major depressive disorder. The Turkish adaptation of the scale was conducted by Sarı et al. [72]. The higher scores obtained from the scale indicate higher symptomatology. The psychometric properties of the scale showed acceptable results. The Cronbach's alpha for the Turkish version was reported as .84.

##### Generalized Anxiety Disorder-7 (GAD-7) Turkish form

2.9.1.2

GAD-7 was developed by Spitzer et al. [73] to measure anxiety disorder symptoms. The Turkish adaptation of the scale was conducted by Konkan et al. [74]. The higher scores obtained from the scale indicate higher symptomatology. The Cronbach's alpha for the Turkish version was reported as .85.

##### The brief adjustment Scale-6 (BASE-6) Turkish form

2.9.1.3

BASE-6 was developed by Cruz et al. [75] to gauge general psychological distress and adjustment. A Turkish adaptation of the scale was conducted by Yıldırım and Solmaz [76] with a sample consisting of university students. The internal consistency of the scale was reported as .88.

##### Attitudes toward internet-based interventions scale (ETAM) Turkish form

2.9.1.4

The ETAM was developed by Apolinário-Hagen et al. [77] to gauge people's opinions about internet-based interventions as a substitute for traditional in-person psychotherapy. Higher scores obtained from the scale indicate more positive attitudes. The Cronbach's alpha of the scale in the original study was reported as .92. A Turkish adaptation study of the scale was conducted by Özer et al. [78] and the internal consistency was reported as .86.

#### Other measures

2.9.2

##### Demographic information form

2.9.2.1

A demographic form created by the researchers to gather information about the demographics of the participants, including their age, gender, current psychiatric diagnosis (if any), and history of psychiatric treatment/help.

##### System usability scale (SUS-10) Turkish form

2.9.2.2

SUS-10 aims to assess the impact of program usability on treatment outcomes [79]. The higher scores obtained from the scale indicate better program usability. The Turkish adaptation of the scale was conducted by Kadirhan et al. [80]. Cronbach's alpha was reported as .78.

##### Module evaluation

2.9.2.3

At the end of each module completed, the participants will be asked to rate the effectiveness of the module on a single question (0- not effective, 10-very effective). The overall program evaluation will be made based on the sum of these scores.

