### Procedure

2.3

Posters and online announcements of the study will be created and sent to the five universities mentioned above. The project website, advertising posters, academic institutions' websites, and social media sites will all be used to announce the study. Students will be able to navigate to the project website by scanning the QR code on the posters.

Upon accessing the project website, participants will be asked to complete an online informed consent form outlining the study's aims before deciding whether to volunteer. After obtaining the participants' consent to volunteer in the study, they will be requested to fill out the questionnaires. Those who meet the remaining inclusion requirements but score highly on PHQ-9 and GAD-7 or undergoing psychological treatment will not be able to register or access the system. These users will be notified to seek professional help if they so choose, along with a window with contact details for resources (counseling center of the university, medico-social units) that will enable them to receive help at the appropriate university. Allotted participants will get e-mails and SMSs letting them know which group they are in. To guarantee the validity and reliability of our results, we want to take this heterogeneity into consideration during our analysis procedures. The consort flow chart of the study is presented in Fig. 1.

In the qualitative part, to ensure diversity in the semi-structured interview process, participants who discontinued the program with the lowest and highest symptom levels will be invited, while maintaining a balanced gender ratio. This stratified approach aims to capture a wide range of perspectives. The interviews will be conducted by researchers holding doctoral degrees in psychology, ensuring both expertise and consistency in data collection.

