### Randomization

2.4

Through the use of software (randomizer.org), participants who have registered on the project website and fulfilled the inclusion criteria will be assigned to groups randomly. Care will be given to guarantee that the distribution of men and women is equal to achieve maximum variety in each group. Therefore, the randomizer.org website's block approach will be utilized. Participants will remain blinded to their group assignment to minimize bias. Group assignment will be managed by a third party using coded identifiers. Participants in the intervention group will immediately access the program, while those in the waitlist control group will be informed that the program will not start immediately for them but will be made available after a waiting period. Both groups will receive equivalent instructions and communication to ensure they cannot discern their allocation. This approach balances expectations and perceived fairness, reducing potential bias in participant responses.

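### In the trial itself SUS-10 is scheduled only before anyone has used the program, and the overall program evaluation is a sum that mixes perceived effectiveness with the number of modules completed

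*Protocol article*

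**What the plan says.** **Usability.** Section 2.9.2.2 states the purpose: "SUS-10 aims to assess the impact of program usability on treatment outcomes". Higher scores are to mean better usability. The only schedule for the scale is Table 1 in section 2.9. There the row "System Usability Scale (SUS-10") carries a mark under Pilot Study and under T0, and is blank under T1 and T2. Section 2.9 describes the first two assessments as "baseline (T0) for all groups, immediately following program completion (T1; 8 weeks").

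On the order of events, section 2.3 says: "After obtaining the participants' consent to volunteer in the study, they will be requested to fill out the questionnaires". People who score too high on PHQ-9 and GAD-7 at that stage cannot register. Section 2.4 then says: "Participants in the intervention group will immediately access the program". Section 2.8 gives the waitlist arm the unguided version at week 12, after its assessments.

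**Program evaluation.** Section 2.9.2.3 says: "At the end of each module completed, the participants will be asked to rate the effectiveness of the module on a single question", on a scale from 0 to 10. It continues: "The overall program evaluation will be made based on the sum of these scores". Section 2.6 fixes the number: "The intervention will consist of six modules". Nothing in the article averages the ratings, divides by the number of modules completed, or limits the sum to people who finished all six.

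**The concern.** A usability scale asks about a system the respondent has used. If the form is built from Table 1, every trial participant answers it before seeing the program, and the waitlist arm answers it about a program it will not open for twelve weeks. The link between usability and outcome then cannot be studied in the trial, and the missing post-use scores cannot be recovered afterwards.

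The sum has a different problem. Two people who found the modules equally effective get different totals if one stopped earlier, so a low total may mean poor ratings or few modules. The protocol expects early stopping: section 2.5 anticipates 35% dropout, and section 2.9.2.5 plans interviews with people who quit after two modules or fewer. A reader of the overall evaluation could not tell whether it describes perceived effectiveness or retention.

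**Working it through.** The plan states no figure for either measure, so there is none to reproduce. The first part is a check on the order of events, the second a check on the scoring rule.

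**1. Order of events for SUS-10**

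- Consent, then questionnaires, then registration if eligible (section 2.3).
- Random assignment, then immediate access for the intervention arms (section 2.4).
- Waitlist access at week 12 (section 2.8).
- SUS-10 at T0, the baseline for all groups (section 2.9 and Table 1).

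T0 therefore falls before first use in all three arms. No other section gives a later SUS-10 in the trial.

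**2. The scoring rule for one person**

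Inputs: rating 0 to 10 per completed module (section 2.9.2.3); six modules (section 2.6).

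Sum = mean rating × modules completed.

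- Possible range: 0 to 10 after one module, 0 to 20 after two, 0 to 60 after six.
- Two modules rated 10: 2 × 10 = 20. Six modules rated 4: 6 × 4 = 24. The lower rating gets the higher total.
- Rating 7 throughout: 6 × 7 = 42 for a completer, 2 × 7 = 14 for someone who stops after two.
- Among people who complete all six, the sum is 6 × the mean and carries the same information.

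**3. The scoring rule for a group**

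Expected sum = r × [(1 − d) × 6 + d × k], where r is the mean rating, d the proportion who drop out and k the modules they complete. The value of d comes from section 2.5, taken here as the share who do not finish all six modules. Values of r and k are assumptions.

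With r = 7 and d = 0.35:

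| k | Calculation | Mean sum |
|---|---|---|
| 1 | 7 × (3.9 + 0.35) | 29.75 |
| 2 | 7 × (3.9 + 0.70) | 32.2 |
| 3 | 7 × (3.9 + 1.05) | 34.65 |

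With no dropout the figure is 42. Over the 2% to 83% dropout range cited in section 2.5, with k = 2, it runs from 7 × (5.88 + 0.04) = 41.44 to 7 × (1.02 + 1.66) = 18.76. The mean rating per completed module is 7 in every case.

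**4. If two groups with different retention were set side by side** (illustrative dropout of 25% and 45%, k = 2)

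- Equal ratings of 7: 7 × (4.5 + 0.5) = 35.0 and 7 × (3.3 + 0.9) = 29.4. The gap of 5.6 comes from retention alone.
- Ratings of 6.5 and 7.5: 6.5 × 5.0 = 32.5 and 7.5 × 4.2 = 31.5. The order of the ratings is reversed.

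**The case against.** **The SUS-10 timing rests on one table mark.** This is true, and the mark may simply sit in the wrong column. But the row keeps its empty cells like its neighbours, so an extraction fault is unlikely, and no text overrides it. If it is a misprint, it still conflicts with section 2.9.2.2 and needs correcting before the form is built.

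**A reader might infer that all SUS-10 data will be uninterpretable.** The documents do not support that. Nothing in them casts doubt on the pilot scores. The pilot cannot, however, link usability to outcomes in the trial.

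**A reader might infer that the trial's guided-unguided comparison is biased.** No arm comparison of the module sum is planned. Section 2.10 names depression, anxiety and adjustment as the outcomes and analyses neither the sum nor SUS-10. The side-by-side figures show what the sum would do if it were used that way.

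**A reader might infer that a claimed strength of the study collapses.** The Discussion says acceptability and usability were neglected in earlier research, but the strength it draws is the ability to identify causes of early dropout. That rests mainly on the interviews in section 2.9.2.5. The interviews in section 2.9.2.4 also ask about experience after use. Nor is either scale described as a measure of acceptability: one concerns usability, the other effectiveness.

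**Table 1 places module evaluation at T1, while the text collects it after each module.** This is clerical. The table has no column for the treatment period and the text is clear.

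**A mean is not a complete cure.** This stands. A mean covers only modules a person finished, it will be flattering if dissatisfied users stop, and modules differ in content. The fix allows for this.

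**Conclusion.** The point holds on two limited counts. In the trial, SUS-10 is scheduled only before use, which contradicts its stated purpose; this follows from the order of events and needs no assumption beyond reading the Table 1 row as printed. The overall program evaluation mixes perceived effectiveness with the number of modules completed whenever completion differs, as the expected dropout implies. At 35% dropout and a constant rating of 7, the group mean falls from 42 to between 29.75 and 34.65; the size depends on the assumed rating, on dropouts completing one to three modules, and on reading the 35% as the share who do not finish all six.

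Both measures stand under other measures in section 2.9.2. The primary analyses of PHQ-9, GAD-7 and BASE-6 and the sample size are unaffected. The correction is still worth making. Module ratings could be rescored later if they are stored one by one, but a usability score not collected after use cannot be.

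**What to change.** 1. In Table 1, move the trial administration of SUS-10 from T0 to T1, for the guided and unguided arms only, including participants who stopped after some use. Section 2.9 already sends the T1 assessment to everyone whether or not they finished, so no new contact is needed. Leave the pilot administration as it is.
2. In section 2.9.2.3, replace the sum with the mean rating per completed module. Report the number of modules completed by arm beside it, and show ratings by module and by completion status, because the mean covers only finished modules. A person who completed none has no mean and appears only in the completion count.
3. While editing Table 1, a note that module ratings are collected after each module would remove the clerical mismatch.

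Cost: one form moved in the online system, one scoring line changed, ten more items at T1 and ten fewer at T0, and slightly more reporting.

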##### User experience on program effectiveness

2.9.2.4

Qualitative approaches will be used to assess program participants' experiences. Following the use of quantitative measures to evaluate the participants' progress, those who demonstrated the highest and lowest levels of progress will be invited to an online, semi-structured interview. This will be determined by calculating the difference between the participants' pre-and post-test results. To find out more about the user experience, a total of 16 participants—eight from the group with the highest improvement and eight from the group with the lowest improvement—will be asked to provide information about their experiences to learn more about the effectiveness of the internet-based self-help platform. The example questions include “How was your experience with the self-help platform?" and “What were the advantages and disadvantages of the self-help platform?”

##### User experience on dropout

2.9.2.5

Participants who completed at most two modules -or less-among those who have quit using the platform will be the subject of a semi-structured qualitative interview to learn more about the experiences that caused them to drop out early. 16 dropout participants -eight participants from the guided group and eight participants from the unguided group-will be chosen at random based on their ID numbers using the randomizer.org website. The semi-structured interview questions will focus on challenges faced while using the program, reasons for early discontinuation, and features participants believe could have encouraged them to continue. The example questions include “Can you explain the reasons why you quit using the platform?" and “What were the problems that you faced while using the platform?” Based on these key questions, the participants will be interviewed using probes to get more useful responses. This approach seeks to gather comprehensive insights to improve the program's design and accessibility.

### Statistical analyses

2.10

A Mixed ANOVA will be employed to analyze the data, with Group (Guided, Unguided, Control) as the between-subjects factor and Time (Baseline, Post-Test, Follow-Up) as the within-subjects factor. This approach will assess both the main effects of Group and Time, as well as the interaction effect between Group and Time on the primary outcomes—changes in depression, anxiety, and adjustment levels. Post-hoc tests will be conducted to explore significant interactions. If necessary, covariates will be included in the analysis through a Mixed ANCOVA to adjust for baseline differences.

Dropout and missing data are anticipated in the study. To address this, missing data will be handled using relevant methods, e.g., multiple imputation or Multilevel Mixed-Model Regression Analysis, depending on the nature and pattern of missingness. Multiple imputation will be employed to estimate missing values if the data are missing at random, while Multilevel Mixed-Model Regression Analysis will be applied to account for both missing data and repeated measures over time. Baseline characteristics across the three groups will be tested using statistical methods such as t-tests, chi-square tests, or ANOVA to ensure comparability. Any significant differences will be adjusted for in subsequent analyses. These approaches will help ensure the robustness of the findings despite anticipated dropout and missing data.

The qualitative data will be transcribed and coded into themes by two independent researchers to ensure reliability. In the analysis of the data, the MAXQDA program will be utilized. According to the principles of [81] to ensure the reliability and validity of the results, the coding and assignment of themes will be conducted by several researchers, and the evaluation will be made through consensus/(disagreement + agreement) ∗100 formula as suggested. At the end of the analysis, consensus and disagreements will be evaluated in a project team meeting.

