### Aims

1.2

This study aims to accomplish two main objectives. The initial goal is to test the effectiveness of the internet-based intervention for university students, UNIPDES, which is based on a transdiagnostic CBT, in raising psychological adaptation levels and improving the depressive and anxiety symptoms in university students, controlling for participants' initial depressive symptoms, anxiety, psychological adjustment scores, and attitudes toward internet-based interventions. Consistent with this objective, we seek to evaluate the variations between guided and unguided treatment delivery compared to the waiting list control group.

The second goal is to assess the reasons why users who enroll in internet-based interventions dropout. In order to assess the possible influence of participant attitudes on internet-based therapies on dropout rates, we want to incorporate an analysis of these attitudes into our study. In particular, knowing how people's attitudes, whether favorable or unfavorable, affect their choices to stick with or stop using such interventions can help a researcher to improve their design and execution. Our study aims to add to the body of knowledge on dropout in internet-based interventions in this regard.

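### Aim 1 and the sample size commit to adjusting for four baseline scores, but the analysis section adds covariates only when baseline tests are significant

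*Protocol article*

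**What the plan says.** Section 1.2 (Aims) states the first aim as testing effectiveness while "controlling for participants' initial depressive symptoms, anxiety, psychological adjustment scores, and attitudes toward internet-based interventions". Section 2.5 (Sample size estimation) enters the same four scores as covariates. Neither section makes the adjustment conditional.

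Section 2.10 (Statistical analyses) names a Mixed ANOVA "with Group (Guided, Unguided, Control) as the between-subjects factor and Time (Baseline, Post-Test, Follow-Up) as the within-subjects factor", and the Abstract repeats this without covariates. Adjustment is then made conditional: "If necessary, covariates will be included in the analysis through a Mixed ANCOVA to adjust for baseline differences". The condition appears further on in the same section: "Baseline characteristics across the three groups will be tested using statistical methods such as t-tests, chi-square tests, or ANOVA to ensure comparability", followed by "Any significant differences will be adjusted for in subsequent analyses".

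Table 1 in section 2.9 shows PHQ-9, GAD-7, BASE-6 and ETAM all collected at T0.

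**The concern.** The article gives two different rules for the same primary analysis: fixed adjustment in sections 1.2 and 2.5, and adjustment by trigger in section 2.10. A reader cannot tell in advance which model will produce the reported result.

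The trigger is poorly chosen. Under randomisation a significant baseline difference is a chance event, so testing selects covariates by accidental imbalance and not by how well they predict the outcome. With three primary outcomes, the rule could also give each a different model, settled after the data are seen.

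There is a structural difficulty too. Baseline is already one of the three repeated outcomes. If the covariate that is triggered happens to be that outcome's own baseline score, the same measurement is both outcome and covariate, and section 2.10 does not say how that would be handled.

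Finally, a Group × Time test uses baseline through change from baseline. This is generally less efficient than adjusting for it.

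**Working it through.** **1. The plan's own figure.** Section 2.5 gives a minimum of 244 for three groups, four covariates, 80% power and a 5% level. The printed effect sizes (d = 4, f = 2) fit only if read as 0.4 and 0.2; taken literally, f = 2 gives N = 10. For a three-group ANCOVA with four covariates, λ = f²N = 0.04 × 244 = 9.76 with 2 and 244 − 3 − 4 = 237 degrees of freedom. Power is 0.8001, against 0.7984 at N = 243, so 244 is reproduced. At f = 0.2 and correlations 0.3/0.5/0.7, a repeated-measures interaction gives 73/53/33 and a repeated-measures between-group test gives 132/164/196. The stated N therefore matches a between-group test of ANCOVA type. It does not match the Group × Time test in section 2.10. The covariate count itself does not matter here: with no covariates N is also 244.

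**2. How often chance triggers adjustment.** For the four named scores at the 5% level, if independent: 1 − 0.95⁴ = 0.185, about 19%. The scores are probably positively correlated, which lowers this; the limit under perfect correlation is 5%.

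**3. Variance.** With unit variance and within-person correlation ρ, a change score has residual variance 2(1 − ρ) and a baseline-adjusted score 1 − ρ². The ratio is 2/(1 + ρ): 1.54, 1.33, 1.25, 1.18 and 1.11 at ρ = 0.3, 0.5, 0.6, 0.7 and 0.8. It exceeds 1 for every ρ below 1.

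**4. Power.** Assumptions: 71 per arm (330/3 = 110, and 110 × 0.65 = 71.5), so N = 213; both programs 0.4 SD better than control at T1 and T2; equal correlation between all visits; and no further gain from the other three covariates. The article gives no ρ, so a range is shown.

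Group means of 0.4, 0.4 and 0 give f² = (0.1333² + 0.1333² + 0.2667²)/3 = 0.03556, and Nf² = 7.573.

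- Group × Time over three visits: λ = 7.573 × (2/3)/(1 − ρ), df 4 and 2 × 210 = 420.
- Baseline-adjusted T1: λ = 7.573/(1 − ρ²), df 2 and 209.
- Baseline-adjusted mean of T1 and T2: λ = 7.573/[(1 + ρ)/2 − ρ²], df 2 and 209.

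| ρ | Group × Time: λ, power | Adjusted T1: λ, power | Adjusted T1 and T2: λ, power |
|---|---|---|---|
| 0.3 | 7.21, 55% | 8.32, 73% | 13.52, 92% |
| 0.5 | 10.10, 71% | 10.10, 81% | 15.15, 94% |
| 0.6 | 12.62, 82% | 11.83, 87% | 17.21, 97% |
| 0.7 | 16.83, 92% | 14.85, 94% | 21.04, 99% |
| 0.8 | 25.24, 99% | 21.04, 99% | 29.13, above 99% |

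The like-for-like comparison is the first column against the last, since both use T1 and T2. The middle column uses one post-baseline visit and still matches or beats the planned test throughout.

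**5. Type I error.** In simulations under no effect (3000 runs per setting, 81 per arm, ρ = 0.3, 0.5 and 0.7), rejection rates were about 0.04 to 0.06 throughout. This covers the planned Group × Time test, the version with baseline as both outcome and covariate (0.053 to 0.062), and a simplified conditional rule: the T1 score compared unadjusted unless baseline differs significantly (0.038 to 0.046).

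**The case against.** The strongest reply is that the loss may be small. It rests on a correlation the article does not state; at 0.6 the planned interaction already has 82% power, and at 0.8 nothing measurable is lost against the adjusted T1 test. The 71 per arm is also a complete-case figure. Section 2.10 plans multiple imputation or a multilevel model, and T1 goes to everyone whether or not they finish the program. At 81 per arm and ρ = 0.5 the interaction has about 78%. All of this stands, and it is why the loss is given as a range.

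Several stronger readings are tempting, and the article does not support them.

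- *That the Group main effect, which averages in the pre-treatment visit, is the plan's test.* Its power is only about 51% at ρ = 0.5 in the setting above. But section 2.10 defines the outcomes as changes and follows up significant interactions, so the treatment question rests on Group × Time. Baseline is used inefficiently; it is not ignored.
- *That adjustment always puts baseline on both sides of the model.* This happens only if the triggered covariate is that outcome's own baseline score. A trigger on age or ETAM would not do it.
- *That chance triggers adjustment about a third of the time.* That needs eight independent variables (1 − 0.95⁸ = 0.34). Section 2.10 lists none, and only four are named as covariates elsewhere.
- *That the allocation blocks are faulty.* Section 2.4 says "Care will be given to guarantee that the distribution of men and women is equal" and mentions blocks. How they are drawn is detail a condensed article may leave to the full protocol.

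**Conclusion.** The point holds as a contradiction and a badly fixed rule. Sections 1.2 and 2.5 promise adjustment for four baseline scores; section 2.10 makes it depend on significance tests that, after randomisation, detect only chance. The three primary outcomes could end up with different models.

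A reader might infer that the conditional rule inflates false positives. The check found no material inflation, so that claim should not be made. A reader might also infer that the sample size is wrong because covariates were counted; it is not, since 244 results with none or four. What differs is the model to which f = 0.2 refers.

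The efficiency cost against an adjusted T1 test runs from 18 percentage points at correlation 0.3 to none at 0.8. Against an adjusted analysis of T1 and T2 together, which has about 92% or more throughout, it runs from about 37 points to about 1. These figures assume equal effects at T1 and T2, equal correlation between visits and 71 analysed per arm. The contradiction and the data-driven choice of model depend on none of these assumptions.

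**What to change.** In section 2.10, replace the conditional rule with one fixed model, identical in form for PHQ-9, GAD-7 and BASE-6:

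- T1 and T2 scores as the repeated outcome, with Group, Time and Group × Time;
- always adjusted for the four baseline scores named in sections 1.2 and 2.5 (PHQ-9, GAD-7, BASE-6, ETAM);
- baseline as a covariate and not a level of Time. The treatment question is then carried by the Group differences at T1 and T2, and Group × Time asks only whether they change between those visits. The text should say so.

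Drop the baseline significance tests as a trigger and describe baseline characteristics by arm. Bring the Abstract into line. Gender, which allocation is meant to balance, may be added to the model as an optional extra.

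The cost is a rewording before any outcome comparison is seen. No new data are needed: the four scores and gender are already collected at T0.
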